## Abstract

**Background:**

Neurogenic bladder (NB) can affect people after stroke episodes. NB features changes in the normal voiding pattern at the bladder filling and emptying phases. Overactive NB is characterized by urgency symptoms, with or without urinary incontinence, caused by NB. This disorder affects many domains of life (physical, social, psychological, domestic, sexual) that limit personal autonomy and degrade the quality of life. Among the several treatments available, the conservative physical therapy intervention through tibial nerve electrostimulation (TNES) and parasacral electrostimulation (PSES) can help improve patient conditions with a smaller number of collateral effects than those of interventions based on medication. The aim of the present study is to compare the effects of TNES and PSES techniques in women with overactive NB after stroke episodes to assess the impact of urinary incontinence in these women, on their number of incontinence episodes, daytime and nocturnal urinary frequency, and quality of life.

**Methods:**

This is a prospective clinical study to compare two randomized groups based on parallel and blind conditions. Forty-four women who have had a stroke episode at least 30 days before the trial and who have developed overactive NB will be recruited for the trial. All patients will be subjected to initial evaluation and randomly divided into two groups, TNES and PSES. Subsequently, the two groups will be subjected to a 12-session intervention protocol, twice a week. A new evaluation will be performed after the intervention.

**Discussion:**

The results of this study will contribute to the physiotherapeutic treatment of women with NB after a stroke episode since such results will add information about the benefits of this treatment, urinary control, and the improvements in the quality of life of these women.

**Trial registration:**

Brazilian Registry of Clinical Trials (REBEC) RBR-2bn2z4. Registered on December 11, 2018

## Administrative information

Note: the numbers in curly brackets in this protocol refer to SPIRIT checklist item numbers. The order of the items has been modified to group similar items (see http://www.equator-network.org/reporting-guidelines/spirit-2013-statement-defining-standard-protocol-items-for-clinical-trials/).

## Introduction

### Background and rationale {6a}

Stroke episodes result from the fast development of clinical signs of focal and/or global disorders in brain function. These disorders have ischemic or hemorrhagic vascular origin; therefore, they cause changes in the cognitive and sensory-motor planes, depending on the injured area [1]. Vesico-sphincter disorders can affect people after stroke episodes. Neurogenic bladder (NB) is the most common of these disorders since it can change normal urinary patterns at the bladder filling and emptying phases [2].

NB is featured by normal bladder function losses caused by injuries in parts of the central nervous system or in peripheral nerves involved in urinary control, which can account for changes in such functions and result in hyperactive or hypoactive bladder [2]. Overactive NB is characterized by urgency, with or without urgency urinary incontinence, usually with increased daytime frequency and nocturia in the setting of a clinically relevant neurologic disorder with at least partially preserved sensation [3].

Urinary incontinence (UI) after a stroke episode is frequent; in addition, UI is a strong predictor of poorly functioning prognostics [4]. Stroke-related compromised urinary function depends on the degree, size, and site of the injury, but approximately 80% of UI cases can affect the lower urinary tract [2]. UI affects several domains of life (physical, social, psychological, domestic, and sexual) since it limits personal autonomy and degrades the quality of life [4]. Diagnosis and the correct treatment of bladder dysfunction are essential to improve patients’ well-being, to prolong their survival, and to reduce sequels [2].

Using anticholinergic medication to treat hyperactive NB improves disease symptoms [5], but its long-term use is limited by patients’ tolerance to the treatment [6]. Previous studies have reported collateral effects such as intestinal constipation [6, 7], dry mouth, heat intolerance [5], and incomplete urination [6]. Botulinum toxin A is another option to treat NB. It can be used to treat vesico-sphincteric dyssynergia [8]; however, the cost of this treatment is high, and its duration is limited to 6–9 months [5]. Thus, it is necessary to identify new therapeutic options to replace lower-cost treatments applied to overactive NB symptoms—these options must not trigger systemic collateral effects or compromise bladder emptying [6].

Physiotherapeutic treatment through electrostimulation of the tibial and parasacral nerves has been seen as an option to treat overactive bladder in adult [9–12] and infant [13, 14] patients. However, little is known about the results of these techniques between patients who present NB after stroke episodes. Monteiro et al. [15] observed that electrostimulation of the tibial nerve reduced urinary urgency and frequency in men after stroke episodes. On the other hand, Silva et al. [16] did not find statistically significant differences before and after this treatment in four women who presented NB after a stroke episode in a series of cases.

Given the great number of stroke carriers with overactive NB symptoms and the loss in their quality of life, it is necessary to investigate the most effective conservative treatments against such disorder. It is essential to highlight that, although these techniques are often used in clinical practice, there are no studies comparing the electrostimulation of these two nerves in overactive NB treatment after a stroke episode. In addition, few studies that have analyzed these techniques presented low methodological quality. The analysis of the effects of these techniques on women presenting overactive NB after strokes allows for the adoption of a more accurate treatment to rehabilitate these women. This treatment aims at improving the quality of life of such women since it is of easy application and well accepted by patients, as well as fewer reports of side effects.

### Objectives {7}

The aim of the present randomized trial is to compare the effects of tibial nerve electrostimulation (TNES) and parasacral electrostimulation (PSES) techniques in women with overactive NB after stroke to UI impact on the lives of these patients, to urinary frequency, to the number of urinary losses, and to quality of life. We hypothesize that both groups will present fewer symptoms and that there will be no differences between groups.

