## Interventions

### Explanation for the choice of comparators {6b}

The techniques of TNES and PSES are noninvasive and widely used in clinical practice. No studies were found using this technique in women with NB after stroke. Therefore, we would such as to know which one is more effective for the treatment of poststroke women.

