### Sample size {14}

Studies that applied the techniques to other populations were analyzed to estimate the percentage of improvement in urinary symptoms after application of TNES and PSES. The studies of Malm-Buatsi et al. [26], Monteiro et al. [15], and Kabay et al. [27] were analyzed. Thus, considering a confidence of 99%, a power of the test of 90%, considering the proportion of patients who had improvement after TNES of 69% (PA = 0.69) and patients who had improvement after PSES of 13% (PB = 0.13), the sample size for each group was 22 women. To calculate the sample, Bioestat 5.0 software was used [28].

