## Statistical methods

### Statistical methods for primary and secondary outcomes {20a}

Statistical Package for the Social Sciences (SPSS Statistics version 23) software will be used in the statistical analysis. The Shapiro-Wilk test will be initially applied to assess data normality. Data will be described as the mean (standardized deviation) for normally distributed continuous variables, median (interquartile range) for continuous variables without normal distribution, and frequency (percentage) for categorical variables.

For parametric data, comparison between the groups will be carried out using the analysis of variance (ANOVA) test. Significance values lower than 0.05, at the 95% confidence interval, will be interpreted as statistically significant. The clinical relevance of recorded values will be confirmed through effect-size calculations (Cohen’s *d*) based on significant differences. The following effects will be taken into account: 0.00 to 0.49, low; 0.50 to 0.79, medium; and above 0.80, high [32]. The intention-to-treat analysis will be carried out [31].

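### The protocol hypothesises no difference between techniques, but its sample size and its only test are built to detect a difference, so the planned analysis cannot support that hypothesis

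*Protocol article*

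**What the plan says.** Four sections of the protocol article bear on the between-group comparison.

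- **Objectives {7}**: the aim is to compare TNES with PSES, followed by the prediction "We hypothesize that both groups will present fewer symptoms and that there will be no differences between groups".
- **Explanation for the choice of comparators {6b}**: the reason for the comparison is "to know which one is more effective for the treatment of poststroke women".
- **Sample size {14}**: 69% are assumed to improve after TNES, against "patients who had improvement after PSES of 13% (PB = 0.13), the sample size for each group was 22 women". Confidence is set at 99% and power at 90%.
- **Statistical methods for primary and secondary outcomes {20a}**: groups are compared by ANOVA. The decision rule is "Significance values lower than 0.05, at the 95% confidence interval, will be interpreted as statistically significant". Cohen's d is tied to significant differences.

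The primary outcome is change in ICIQ-SF, scored 0 to 21. The article gives no equivalence or non-inferiority margin and no confidence-interval rule for concluding that the techniques are similar.

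**The concern.** The three statements of purpose disagree. The hypothesis predicts no difference, the rationale asks which technique is better, and the sample size assumes a very large difference in favour of TNES. A 13% response to PSES also sits badly with the expectation that both groups improve and end up alike. An analysis plan could add detail, but it could not make the hypothesis and the sample-size assumption agree.

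A test of difference can reject equality; it cannot establish it. The protocol gives no other rule by which its hypothesis could be supported. There is no sham or untreated arm, so improvement in both arms together with p≥0.05 would match the Objectives exactly. Because Cohen's d is tied to significant differences, the stated plan calls for no effect size after a null result, which is when readers most need to see how large a difference remains possible. The Discussion says the results should help physical therapists' clinical decisions, so the two techniques could be treated as interchangeable on weak evidence.

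**Working it through.** **Inputs from the protocol article:** 22 per arm, 1:1 allocation; improvement of 69% and 13%; 99% confidence and 90% power in the sample size; significance at 0.05 in the analysis.

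**Assumptions:** no dropout, roughly normal ICIQ-SF change and a common SD. The article gives no ICIQ-SF SD and no margin, so results are in SD units over a range. With two groups, ANOVA on change is equivalent to a two-sided t-test.

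**1. The plan's own figure.** The gap is 0.69 − 0.13 = 0.56 and the mean proportion is 0.41. The pooled two-proportion formula, two-sided at 0.01 with 90% power, is

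n = [2.576·√(2·0.41·0.59) + 1.282·√(0.69·0.31 + 0.13·0.87)]² / 0.56² = 20.3, so 21 per arm.

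With continuity correction it gives 24; one-sided with correction, 22. The stated 22 is reproduced to within 2 women. The arithmetic is sound, and it is a calculation for detecting a difference.

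**2. Chance of a non-significant result when the techniques differ.** The standard error is √(2/22) = 0.3015 SD, with 42 degrees of freedom and critical t = 2.018. The noncentrality is d/0.3015.

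| True difference | Noncentrality | Power | P(p≥0.05) |
|---|---|---|---|
| 0.3 SD | 0.99 | 16% | 84% |
| 0.5 SD | 1.66 | 37% | 63% |
| 0.8 SD | 2.65 | 74% | 26% |
| 1.0 SD | 3.32 | 90% | 10% |

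**3. What a null result leaves open.** The 95% interval half-width is 2.018 × 0.3015 = 0.61 SD. For an assumed ICIQ-SF SD of 4 to 6 points, that is 0.608 × 4 = 2.4 to 0.608 × 6 = 3.7 points.

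**4. Chance of showing equivalence when the arms are identical.** Equivalence within ±m needs the whole interval inside the margin, so |estimate| + t × SE < m. Two one-sided 5% tests correspond to a 90% interval (t = 1.682, half-width 0.51 SD). A 95% interval is stricter.

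| Margin | 90% interval (two one-sided 5% tests) | 95% interval |
|---|---|---|
| 0.5 SD | 5% | 0.4% |
| 0.9 SD | 80% | 66% |

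By a normal approximation, 80% power at a 0.5 SD margin with two one-sided 5% tests would need 2 × (1.645 + 1.282)² / 0.5² = 68.5, so 69 per arm.

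**The case against.** The strongest reply is that the harm is inferred. The protocol says only how p<0.05 will be interpreted and gives no rule for p≥0.05. The sentence in the Objectives can be read as the investigators' expectation, set beside a plain comparative aim. A test of difference fits that aim, the rationale and the sample size. This stands in part: a reader might infer that the protocol commits to reading non-significance as equality, and it does not. What remains is a formal hypothesis that nothing in the analysis could support, and an evident risk that a null result is presented as supporting it.

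Three other stronger readings also fail.

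- A reader might infer that a null result is the usual outcome whenever the techniques differ. That is true of small to moderate differences only; power is 74% at 0.8 SD and 90% at 1.0 SD. The article gives no minimal important difference, so whether 0.3 to 0.5 SD matters clinically is open.
- A reader might infer that 44 women can say nothing about similarity. An estimate near zero would exclude large differences, and a margin of about 0.9 to 1 SD is within reach.
- A reader might infer that the trial must be enlarged. The calculation already serves a difference question, so a difference aim needs no new number.

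The sample size also uses a binary improvement rate and a 0.01 level, while the analysis uses a continuous score and 0.05. Those are separate matters and add no weight here.

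**Conclusion.** The point holds as an internal contradiction: the Objectives state a no-difference hypothesis, while the rationale, the sample size and the analysis all address a difference. As written, the plan has no means of supporting its own hypothesis.

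The size of the problem depends on the true difference and on the margin. Up to about 0.5 SD, a null result is more likely than not, and equivalence within such a margin is almost out of reach. Only a margin of about 0.9 to 1 SD could be supported with useful power. These figures rest on complete data, normal outcomes and a common SD; losses to follow-up would make them worse. The documents support a risk of misreading, not a stated intention to equate non-significance with equality.

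**What to change.** Make three changes by a dated amendment through the ethics committee and the registry, as the protocol's own amendment section requires. Recruitment began in January 2019, and patients and the treating researcher know the allocation, so the deadline should be before any between-group data are examined.

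1. **Objectives {7}**: replace the no-difference hypothesis with one two-sided aim, namely whether change in ICIQ-SF differs between TNES and PSES. This agrees with the comparator rationale and with the difference-based sample size.
2. **Statistical methods {20a}**: report the between-group difference and the effect size with a 95% confidence interval whatever the p-value. State that a non-significant result is inconclusive and is not evidence of equality.
3. **Similarity**: make no such claim unless the same amendment fixes a justified margin and an interval level (90% for two one-sided 5% tests). State there that 44 women could support only a margin of about 0.9 to 1 SD.

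The cost is wording and one amendment. The number of women, the randomisation, the outcome and the test stay as they are. The downside is a weaker claim after a null result.

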### Trial design {8}

This is a single-blind randomized controlled trial to compare two randomized groups in parallel (1,1). This article has been written in accordance with the SPIRIT (Standard Protocol Items: Recommendations for Interventional Trials) guidelines.

## Methods: participants, interventions, and outcomes

### Study setting {9}

The trial will be carried out in the facilities of the Sports and Physical Therapy School in the Laboratory of Kinesio-Functional Pelvic Development and Women’s Health of the Federal University of Uberlândia, Brazil.

### Eligibility criteria {10}

Participants presenting the following features will be included in the trial:
Age group 40–70 years;Ischemic or hemorrhagic stroke;To have had a stroke episode at least 30 days before the trial;Overactive bladder after a stroke episode, proven in the medical report;Lack of infection in the urinary tract and bladder tumor; andAbsence of cognitive deficits [17]. The instrument known as Mini-Mental State Examination (MMSE) will be applied to indicate whether the patient presents some traces of cognitive impairment at the initial evaluation. The instrument is divided into seven dimensions, including time orientation, spatial orientation, immediate memory, attention, calculation, evocation, language, and visual construction. The total MMSE score ranges from 0 to 30 points. The instrument was validated to Portuguese from Brazil [18]. Only participants who reach values above 18 will be included in the study [17].

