#### Exclusion criteria

Patients presenting the following features will be excluded from the trial:
Pregnant women;Women who already presented UI before a stroke episode;Women who have a pacemaker implant;Women who use medication to treat NB; andWomen who have undergone medical treatment with botulinum toxin to treat NB.

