### Outcomes {12}

#### Primary outcome measure

The primary outcome measure is any changes in the International Consultation on Incontinence Questionnaire-Short Form (ICIQ-SF) from baseline to final evaluation. The ICIQ-SF questionnaire is simple and fast (only four questions), and it will be used for UI impact evaluation. This questionnaire has general scoring ranging from 0 to 21 points; the closer to 21 points the score is, the stronger the impact of urinary losses on quality of life [11, 20].

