#### Secondary outcome measures

The secondary outcomes of the study are urinary frequency during the day and night, number of incontinence episodes, and quality of life. A bladder diary was used to assess urinary habits in order to quantify daytime and nocturnal urination frequency and episodes of incontinence. Volunteers will be oriented to fulfill a table with this information, provided by the researchers, for 3 days [21].

The World Health Organization Quality of Life – BREF (WHOQOL-BREF) questionnaire will be used to assess the quality of life before and after the intervention. This instrument was developed by the World Health Organization and is based on the quality of life concept, which encompasses positive (medication mobility, played role, satisfaction) and negative points (fatigue, pain, medication dependence, and negative feelings) [22]. The questionnaire comprises 26 questions with 5 coordinated options. There are 24 questions in the four domains (physical, psychological, social relationships, and environment) composing the original instrument and two general questions regarding the quality of life [23, 24]. Each specific domain is assessed based on values found through the WHOQOL-BREF—the higher the score is (maximum = 100), the better the quality of life related to that domain [25].

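### Eligibility admits women with overactive bladder but no incontinence, while the primary outcome scores only urinary losses; any such women would dilute a true difference between arms

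*Protocol article*

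**What the plan says.** All places are in the Protocol article.

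- **Eligibility criteria {10}**: the bladder criterion is "Overactive bladder after a stroke episode, proven in the medical report". No item asks for current incontinence or a minimum ICIQ-SF score.
- **Background and rationale {6a}**: "Overactive NB is characterized by urgency, with or without urgency urinary incontinence". The Abstract defines the condition the same way.
- **Exclusion criteria**: incontinence appears once, to exclude "Women who already presented UI before a stroke episode". Being continent after the stroke is not an exclusion.
- **Primary outcome measure**: "The primary outcome measure is any changes in the International Consultation on Incontinence Questionnaire-Short Form (ICIQ-SF) from baseline to final evaluation". Of the questionnaire it says that "it will be used for UI impact evaluation". It also says "This questionnaire has general scoring ranging from 0 to 21 points", and that "the closer to 21 points the score is, the stronger the impact of urinary losses on quality of life".
- **Secondary outcome measures**: these include the "number of incontinence episodes", which also registers only leakage, beside urinary frequency and WHOQOL-BREF, which do not depend on it.
- **Objectives {7}**: the authors expect both arms to improve and the arms not to differ.
- **Sections {18b}, {20a}, {20b} and {20c}**: the analysis is by intention to treat, and no additional analyses are planned.

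**The concern.** The entry condition and the primary outcome cover different things. Urgency and frequency without leakage are enough to enter, but the primary score responds only to leakage. A continent participant has no room to improve on it, whichever technique she receives and however well it works on her urgency.

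Her expected contribution is a change near zero in either arm. If one technique is better, the average difference shrinks roughly in proportion to the share of such women, and the change scores become a mixture with a cluster at zero. With 22 women per arm there is little power to spare. Because the hypothesis is that the arms do not differ, a non-significant result would be read as support, and the reader could not tell similar techniques from participants who could not register a benefit.

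**Working it through.** **1. Can a continent woman enter?** Taken together, the inclusion criterion, the protocol's definition of the condition and the exclusion list do not stop her. The planned analyses do not separate her afterwards.

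**2. The plan's own sample size.** Inputs from Sample size {14}: improvement rates 0.69 and 0.13, 99% confidence (alpha 0.01), power 90%, stated result 22 per group.

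n = [z(1−α/2)·√(2p̄(1−p̄)) + z(0.90)·√(p1(1−p1) + p2(1−p2))]² / (p1−p2)²

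With p̄ = 0.41: (2.576 × 0.6956 + 1.282 × 0.5718)² / 0.56² = 20.3, so 21. A two-sided test with continuity correction gives 24, and a one-sided test with correction gives 22. The stated 22 is reproduced within the usual spread of formulas.

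**3. Dilution on those rates.** Assume that a share f of women is continent and cannot count as improved, and that the protocol's rates apply to the rest. Both rates are then multiplied by (1−f). Power at 22 per arm is

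Φ{[(p1−p2)·√22 − z(1−α/2)·√(2p̄(1−p̄))] / √(p1(1−p1) + p2(1−p2))}

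For f = 0.20 and alpha 0.01: p1 = 0.552, p2 = 0.104, and (0.448 × 4.690 − 2.576 × 0.664) / 0.5835 = 0.67, so power is 0.75.

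| f | Rates | Difference | Power, alpha 0.01 | n per arm for 90% power, alpha 0.01 | Power, alpha 0.05 |
|---|---|---|---|---|---|
| 0 | 0.690 / 0.130 | 0.560 | 0.93 | 21 | 0.986 |
| 10% | 0.621 / 0.117 | 0.504 | 0.85 | 25 | 0.961 |
| 20% | 0.552 / 0.104 | 0.448 | 0.75 | 31 | 0.915 |
| 30% | 0.483 / 0.091 | 0.392 | 0.63 | 38 | 0.845 |

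**4. Dilution on a continuous change score**, which is how the primary outcome is defined. The documents give no SD or target difference, so these are assumptions: among incontinent women the change has SD 1, mean improvement 1.0 in the reference arm and 1.8 in the other (d = 0.8); continent women change by exactly 0; two-sided alpha 0.05.

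The difference becomes 0.8(1−f). The variance in an arm with mean μ among incontinent women becomes (1−f)(1+μ²) − [(1−f)μ]². For f = 0.20:

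- Difference: 0.8 × 0.8 = 0.64
- Variances: 0.8 × 4.24 − 1.44² = 1.318 and 0.8 × 2 − 0.8² = 0.960
- Pooled SD: √1.139 = 1.067
- Standardised difference: 0.64 / 1.067 = 0.60

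Power from 20,000 simulated two-sample t tests per row:

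| f | All randomised | Only women with room to improve |
|---|---|---|
| 0 | about 74% | – |
| 10% | about 61% | about 69% |
| 20% | about 49% | about 63% |
| 30% | about 39% | about 57% |

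If the assumed reference improvement runs from 0.5 to 1.5 SD, power at 20% continent runs from about 56% to 42%. The direction does not depend on that choice; the size does.

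**The case against.** - **No such women may be enrolled.** The aim speaks of incontinence impact and urinary losses, and excluding pre-stroke incontinence suggests that new post-stroke incontinence was in mind. This shows intent, but no criterion puts it into effect. It does stand against treating 20% or 30% as likely: if the share is near zero, so is the harm.
- **Zero change is an extreme assumption.** The questionnaire items are not printed, so a baseline at or near 0 is inferred from the article's description of the score. A woman at the floor could also get worse, and the adverse event section allows for increased symptoms. This stands as a limit on the figures.
- **A reader might infer bias toward no difference.** The documents do not support that. Eligibility is applied before randomisation and equally to both arms, so the comparison is unbiased for the population as defined. Dilution arises only if a true difference exists; if the techniques are equal, there is nothing to dilute.
- **The loss depends on the scenario.** On the protocol's responder rates at the analysis alpha of 0.05, power is still 0.845 at 30% continent, far above the 39% of the continuous scenario. This stands. Those rates come from other populations and describe improvement in urinary symptoms, not ICIQ-SF change, so they are no firm guide either.
- **A reader might infer that the primary analysis set should be cut to women with baseline incontinence.** That would drop randomised women from a trial committed to intention to treat, after recruitment began in January 2019. Baseline status does not depend on allocation, so a restricted set is valid as a sensitivity analysis, but the case for making it primary is debatable.

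**Conclusion.** The point holds as a mismatch between eligibility and primary outcome, with a conditional consequence. Continent women are eligible, the primary outcome and one secondary outcome cannot show them improving, and nothing in the planned analysis identifies them. If the arms truly differ, each such woman dilutes the difference and costs power at 22 per arm, which makes a null result harder to interpret.

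The size is unknown because the share of such women is not documented. The power losses in the two tables are illustrations. They rest on the assumed shares, on zero change in continent women and, for the continuous case, on d = 0.8 and a 1 SD reference improvement. The documents do not show that continent women have been enrolled in number, nor that the treatment estimate is biased.

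**What to change.** 1. For women still to be recruited, add to Eligibility criteria {10} that urinary incontinence is present at baseline, defined as baseline ICIQ-SF above 0. Use this one definition throughout.
2. Keep all randomised women in the intention-to-treat primary analysis, and adjust for baseline ICIQ-SF.
3. Report by arm the number of women at the floor at baseline.
4. Before unblinding, prespecify a sensitivity analysis restricted to women with baseline ICIQ-SF above 0.

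A threshold just above 0 does not remove the floor altogether, since a very low score leaves little room to improve, and restriction recovers only part of the lost power (39% to about 57% at 30% continent). Baseline adjustment takes account of differing starting scores but does not create room to improve.

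The cost is an amendment by the route in section {25}, a slightly narrower population and possibly slower recruitment. ICIQ-SF is already collected at baseline, so no new measurement is needed, though it must be scored before inclusion is confirmed. The Trial status section describes recruitment as not yet complete, so the criterion could still apply to the remaining women.
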